**Fig. 1 Fig1:**
[figure not shown]
Emergency Department Mental Health Clinical Pathway algorithm

The overall aim of our project is to implement and evaluate impact of the EDMHCP in specific settings and to evaluate the implementation process. The purpose of this paper is to document the protocol for this 3-year mixed methods health services research project. Research objectives for this study are to:Implement the EDMHCP using a theory-driven, evidence-based approach. The pathway will be implemented in four dyads of organizations, each dyad comprising an ED and an associated CMHA.Evaluate clinical pathway effectiveness through measurement of process and service outcomes. Our hypothesis is that a successfully implemented EDMHCP will lead to improved process and service outcomes.Conduct a process evaluation of the pathway implementation strategy to assess the fidelity of the intervention delivered against the outcomes observed.

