### Sampling

#### Setting and site selection

To assess EDMHCP feasibility in various settings, implementation will occur in a staggered process in four Ontario exemplar ED-CMHA dyads with different patient populations and workflows that do not currently utilize clinical pathways. Our exemplar ED sites include a pediatric specialized center with an annual patient census of 70,000, a high-volume community urban hospital (annual patient census 75,000), a low-volume rural hospital (annual patient census 25,000), and a high-volume general hospital in a smaller community (annual patient census 60,000).

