### Project phases

The project phases and designated timelines are outlined in Table 2. Once REB approval is secured at each site, the *pre-implementation phase* will proceed with the site readiness visits and qualitative interviews that will determine the final tailored intervention strategies. The *implementation phase* for each dyad begins with a process to secure a written memorandum agreement between the ED and CMHA to ensure clarity of responsibilities and expectations integral to the pathway. Implementation will proceed as per the tailored intervention strategy. Completed pathway implementation requires, at a minimum, the following: EDMHCP site customization and committee approvals, delivery of at least two educational workshops for each organization, and EDMHCP availability in the ED. We have designated an 8-month period for EDMHCP implementation within each dyad. Following initiation within the first dyad, subsequent dyads will begin implementation in a staggered pattern every 3 months to allow for optimal study team support and incorporating learning from experience with previous dyads. In the *post-implementation phase*, qualitative interviews will explore experience with the implementation and site audits will be done to assess implementation status. We have defined the data collection periods as follows: (i) post-implementation, as the consecutive 9-month span that follows implementation completion plus an initial 3-month “settling in” time and (ii) pre-implementation, as a similar 9-month span prior to the intervention.

**Table 2 Tab2:** Description of project phases

Project phase	Duration	Activities
Pre-implementation	6 months	Site recruitment and REB approvals
		Project launch team meeting
		Site readiness visits
		Qualitative interviews and analysis
		Intervention development
		Site champion training
Implementation	17 months (8 months per dyad)	Site customization
		Forms approvals
		Clinical pathway training
		Adoption and feedback
Post-implementation	12 months	Post-implementation site visits
		Qualitative interviews and analysis
Data collection and analysis	4 months	Chart audits
		Chart to administrative database linkage
		Quantitative data analysis
Follow-up	2 months	Project partner meeting: review of findings
		Wrap-up and dissemination

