#### Health record audits

To evaluate whether the intervention results in EDMHCP use among ED clinicians and documentation of MH-specific discharge recommendations, we will audit health records of relevant patients seen during alternate weeks in each 9-month pre- and post-implementation period. ICD10 codes (F codes, mental, and behavior disorders; X codes, intentional self-poisoning and self-harm; Y codes, poisoning and self-harm of undetermined intent) listed as primary or secondary diagnoses will identify relevant patient charts during the study period. Abstracted data will include demographic and sufficient clinical data to determine risk assessment, disposition plans, and adherence with EDMHCP recommendations. Two auditors, blinded to the study aims and protocol, will be trained to abstract and directly enter health records data into REDCap, an online database [24]. A data dictionary will be created to guide auditors and ensure standardized data collection procedures. Auditors will each abstract the same 50 charts to assess inter-rater agreement. This will be measured for key variables with a kappa coefficient and further training will be done until a prevalence and bias-adjusted kappa >0.6 is achieved.

Based on historical administrative data, the number of pediatric MH visits at the pediatric specialized center is expected to be approximately 2250 during each 9-month period. This sample size will permit estimation of a proportion at this site to within ± 2.1 %, conservatively assuming a true proportion of 50 %. At the other extreme, the lowest number of pediatric MH visits during each 9-month period among the other three sites is expected to be approximately 61 at the rural hospital, which will permit estimation of a proportion to within ±12.5 %. Pooling across sites, the total sample size in each 9-month period is anticipated to be approximately 2503, which will permit estimation of a proportion to within ± 2.0 %.

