### Analysis

#### Quantitative analysis

Descriptive statistics (means and standard deviations for continuous variables or medians with interquartile ranges) will summarize EDs, CMHAs, and patient characteristics. Frequencies and proportions for categorical variables will be reported. We will use a multiple baseline study design and conduct interrupted time-series analysis using segmented regression models, adjusting for site, with ARIMA autocorrelation structure [25–27] to evaluate whether the EDMHCP has resulted in improved health care utilization, medical management, and health sector coordination. Two-sided *p* values less than 0.05 will be considered statistically significant. Model estimates will be tabulated, together with 95 % confidence intervals. We will also calculate hospital level summary measures including proportions in the pre- and post-intervention periods at each site and referred to each CMHA. An unweighted mean of the change from pre- to post-intervention will be calculated for each hospital ED. The main effect measure will be calculated as the difference between the mean changes in intervention.

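### The named main effect is a difference between mean changes, but all four dyads receive the pathway, so there is no second change to subtract and the deciding estimate is left open

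*Protocol article*

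**What the plan says.** The Quantitative analysis section of the Protocol article first sets out the model: "We will use a multiple baseline study design and conduct interrupted time-series analysis using segmented regression models, adjusting for site", with an ARIMA autocorrelation structure. The significance rule follows ("Two-sided *p* values less than 0.05 will be considered statistically significant"), and model estimates are to be tabulated with 95% confidence intervals. The section then adds hospital-level summaries: "An unweighted mean of the change from pre- to post-intervention will be calculated for each hospital ED". It closes with: "The main effect measure will be calculated as the difference between the mean changes in intervention".

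On who receives the pathway, the research objectives in the Background say: "The pathway will be implemented in four dyads of organizations, each dyad comprising an ED and an associated CMHA". Setting and site selection says that "implementation will occur in a staggered process in four Ontario exemplar ED-CMHA dyads". No control, usual-care or non-intervention ED appears anywhere in the article.

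On precision, Health record audits gives half-widths for a single proportion: ±2.1% at the paediatric centre (2250 visits), ±12.5% at the rural hospital (61 visits) and ±2.0% pooled, where "the total sample size in each 9-month period is anticipated to be approximately 2503".

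**The concern.** A main effect defined as a difference between mean changes belongs to a design with intervention and comparison groups. This design has one group, so the definition has a first term and no second.

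The sentence also conflicts with the rest of its paragraph. The Abstract and the start of the Quantitative analysis section assign the question of effectiveness to segmented regression, which handles trend and autocorrelation. The closing sentence gives the label of main effect to a raw summary of site changes, which handles neither. If both stay, a reader cannot tell which number carries the conclusion, and the choice could be made after the results are seen.

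The precision statement does not settle the matter, because it refers to one proportion in one period and not to any change.

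**Working it through.** **1. Is there a second group?** The research objectives, Setting and site selection, and Project phases all describe the same four dyads, and all four implement. That gives 4 intervention EDs and 0 comparison EDs.

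**2. Could the stagger supply a control change?** Inputs from Project phases: "We have designated an 8-month period for EDMHCP implementation within each dyad"; starts 3 months apart; 3 months of settling in; 9-month pre and post windows. With dyad starts at months 0, 3, 6 and 9:
- Pre window = [start − 9, start]: [−9, 0], [−6, 3], [−3, 6], [0, 9].
- Post window = [start + 8 + 3, start + 20]: [11, 20], [14, 23], [17, 26], [20, 29].
- The latest pre window ends at month 9 and the earliest post window begins at month 11, so no post window overlaps another dyad's pre window.

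If the pre window instead ended when implementation was complete (an assumption), the pre windows would be [−1, 8], [2, 11], [5, 14] and [8, 17]. The largest overlap would then be 6 months (dyad 1 post, months 11 to 20, with dyad 4 pre, months 8 to 17). Even so, each dyad has only one change, its own change under the pathway. A contrast between sites would not measure the pathway's effect.

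**3. The plan's own precision figures.** Half-width = 1.96 × √(0.25/n):
- n = 2250: 2.07 points (stated ±2.1%).
- n = 61: 12.55 points (stated ±12.5%).
- n = 2503: 1.96 points (stated ±2.0%).

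All three reproduce, each as the precision of one proportion in one period.

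**4. Precision of the changes that can be computed.** Assumptions: true proportion 50% in both periods, equal counts pre and post, independent visits.
- Pooled pre-post difference: 1.96 × √(2 × 0.25/2503) = 2.77, about ±2.8 points.
- Unweighted mean of four site changes: half-width = 1.96 × (1/4) × √(Σ 0.5/nᵢ). Two counts are given (2250 and 61), which leaves 2503 − 2250 − 61 = 192 visits for the other two sites. Their split is not stated. The rural hospital has the fewest, so the split is taken to run from 96/96 to 62/130.
  - 96/96: Σ = 0.000222 + 0.008197 + 2 × 0.005208 = 0.018836; half-width = 1.96 × 0.25 × 0.13724 = 6.72 points.
  - 62/130: Σ = 0.000222 + 0.008197 + 0.008065 + 0.003846 = 0.020330; half-width = 1.96 × 0.25 × 0.14258 = 6.99 points.
- Health record audits says charts are audited in alternate weeks. If that halves the counts, each half-width grows by √2: pooled about ±3.9 points, unweighted mean about ±9.5 to ±9.9 points.

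These are simple pre-post figures. They do not give the precision of a level or slope change from the regression, which also depends on the trend and autocorrelation terms.

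**The case against.** The strongest reply is that the inferential analysis is intact. The significance rule and confidence intervals come directly after the segmented regression, and the hospital-level summaries come later as an addition. On this view the defect is one badly worded sentence with a misplaced label, in an article that condenses a fuller protocol. Much of this stands: the regression, the four site changes and their average can all be computed. It does not rescue the sentence. The article does state a main effect measure, and states one that its design cannot supply. That is different from leaving a detail to the analysis plan.

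Four stronger readings are tempting, and the documents do not support them.
- *The regression and the site mean must give very different answers, because the paediatric centre supplies 2250/2503 = 89.9% of visits.* The article does not say whether the regression uses visits or site-by-interval proportions, or how intervals are weighted. With unweighted interval proportions and balanced series, the sites would count about equally and the two estimates could be close.
- *The ±2.0% is wrong.* It is correct for what it describes, and the article never claims it for a change.
- *An unweighted mean change for each ED is impossible, because each ED has one change.* Averaging over intervals within an ED is a possible meaning. The wording is unclear, and no more than that.
- *The sentence was carried over from a controlled trial.* Methods/design says the protocol was adapted from an earlier ED pathway protocol, so this is possible, but nothing shows it.

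**Conclusion.** The point holds in this form: the quantity named as the main effect has no second term in a design with four intervention EDs and no comparison ED, and the staggered start does not provide one. The sentence also competes with the segmented regression for the role of deciding estimate. This is an error in the definition of the main effect and should be corrected before data are analysed. It does not mean that the evaluation lacks a workable analysis.

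The conclusion on the missing comparator rests on the text alone. The precision figures are secondary. On the stated counts, about ±2.8 points for the pooled difference and ±6.7 to ±7.0 for the unweighted four-site mean change depend on a 50% proportion, independent visits and, for the latter, the assumed split of 192 visits. The wider figures apply only if alternate-week auditing halves the counts.

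**What to change.** In Quantitative analysis:
1. Delete the closing sentence on the main effect measure.
2. State that the main effect for each primary outcome (process and service) is the site-adjusted segmented-regression intervention effect. Say whether that is the level change, the slope change or both. Keep the trend and autocorrelation terms: a plain post-versus-pre change would lose the planned control for trend. State how sites are weighted.
3. Report the four site-specific pre-to-post changes and their unweighted mean (25% per site) as a named supportive summary, with its own 95% confidence interval.

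In Health record audits, say that ±2.0% is the precision of a pooled proportion in one period. Add the precision of the change, on counts that reflect the alternate-week sampling.

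The cost is rewording and a decision on level, slope and weighting. No new data are needed, and Trial status places the project in pre-implementation. The one drawback is that the precision stated for the effect will look less favourable than ±2.0%.

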### Ethics and registration

Ethics approval for this study has been granted at the coordinating site (Children’s Hospital of Eastern Ontario Research Ethics Board – CHEOREB# 15/146X). Prior to implementation within each dyad, REB approval will be obtained for each site hospital and CMHA. Informed consent will be sought for interviews and focus group meetings. All research data will be stored on a secure server. This trial is registered with ClinicalTrials.gov (NCT02590302).

### Trial status

This project is currently in the pre-implementation phase, seeking local ethics approvals and data sharing agreement, and preparing the intervention strategy.

## Discussion

By operationalizing best evidence into ED practices and formulating ED-CMHA partnerships through explicit agreements, the EDMHCP is poised to address current system gaps in addressing mental health for youth. This clinical pathway will standardize language and care provided through improved communication and explicit expectations for transition between ED and CMHA settings. Our evaluation will also rigorously address requirements for success and inform scalability to other settings. Our research will identify effective strategies to inform EDMHCP adoption in any community and provide knowledge on its impact by evaluating service integration improvements for this vulnerable population.

While trials are more typically conducted with a complete intervention strategy specified in advance, the unique nature of our proposed implementation requires rich understanding of professional and system issues within each organizational context. Hence, the importance of incorporating findings from our qualitative interviews and site visits to optimize likelihood of implementation success.

Important aspects of our tailored intervention strategy include opportunities for providers at each site to identify strengths and barriers to EDMHCP implementation and the deliberate plan to include site leads in the modification process from the beginning. The planned site visits, qualitative interviews, and continued communication will be helpful in generalizing the pathway implementation to other ED and CMHA settings of various sizes, staff, and urban/rural locations. Further, the tailored resources hosted on the HEADS-ED website [16] will be helpful reinforcement for sites that experience a high staff turnover, particularly for new ED residents and staff.

Given the complexity and novel aspects of this intervention, we anticipate some challenges in promoting modifications to current workflows. Each dyad contains the often hectic and somewhat unpredictable ED environment and the variability among CMHAs in their capacity and structure. Additionally, EDs and CMHAs do not typically interact closely, despite the shared patient population that moves between their settings. Other real-life issues such as budget restrictions, staff turnover, and competing project priorities have also been considered in setting our project timelines. At this stage, these issues are not prohibitive for any of our proposed study sites; however, this is always subject to change. Such is the challenge of implementation research.

Our study findings will be relevant for health systems and professionals responsible for ensuring standardized, quality care for children, and youth with acute MH concerns. To ensure our findings directly impact relevant service delivery areas, we have specifically recruited study team members with decision-making authority and/or influence on delivery of care for children and youth with MH concerns. We expect the protocol and findings can be customized and implemented in other EDs and CMHA settings. Equally important, this project will contribute further to implementation evidence relevant to use of clinical pathways and use of theory-based change strategies.

## Abbreviations

CHEO, Children’s Hospital of Eastern Ontario; CMHA, community mental health agency; CSQ-8, client satisfaction questionnaire; ED, emergency department; EDMHCP, Emergency Department Mental Health Clinical Pathway; HEADS-ED, screening tool that includes home, education, activities, drugs, suicidality, emotions, and discharge resources; KI, key informant (interviews); MH, mental health; NACRS, National Ambulatory Care Reporting System; REB, Research Ethics Board; SCA-PI, services for children and adolescents-parent interview; TDF, Theoretical Domains Framework
